### Recruitment {15}

All eligible patients who will be listed for lung transplantation will be asked to participate to the study. A selected team composed by transplant physicians, thoracic surgeons, and one psychologist will talk to the eligible patients at time of screening to explain the aim and design of the study. All possible benefits and risks will be explained to the eligible patients. Since the trial will run in a single-center, a personal relationship with the included patients will help to avoid any possible drop-out due to incompliance.

## Assignment of interventions: allocation

### Sequence generation {16a}

Randomization will be performed with an online software developed by the Medical University of Vienna and already successfully used in several clinical trials. Website: https://cemsiis.meduniwien.ac.at/en/kb/science-research/software/randomizer/

Patients will be stratified according to glomerular filtration rate (GFR) values before randomization (≥ 40–60 ml/min/1.73m^2^, > 60–75 ml/min/1.73m^2^, or > 75–100 ml/min/1.73m^2^) and CMV status (low risk vs high risk). Such stratification will ensure us to equally allocate patients at high risk of kidney dysfunction in the two groups.

### Concealment mechanism {16b}

Randomization will be sequentially numbered. Each patient will be assigned with an alphanumeric code.

### Implementation {16c}

Patients will be screened by [name] and [name]. [name] and [name] will check eligibility of the recipients at randomization time. [name] will perform randomization.

## Assignment of interventions: blinding

### Who will be blinded {17a}

Blinding is not realistically possible in this academic single-center trial. An open-label trial allows concentration-controlled administration of immunosuppressant agents, which have a narrow therapeutic index.

### Procedure for unblinding if needed {17b}

Blinding is not planned

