## Trial design {8}

This trial is a non-blinded randomized prospective trial. Since the dose of immunosuppressive agents will be adapted to reach the blood trough levels, a blinding is not realistically possible. One hundred ten patients respecting the inclusion criteria and exclusion criteria will be randomized into two groups at postoperative day 30. In case of incomplete healing of bronchial anastomosis, patients will be reevaluated for inclusion between postoperative day 30 and 60. Each group will include 55 patients. Patients will be stratified according to glomerular filtration rate (GFR) values before randomization (≥ 40–60 ml/min/1.73m^2^, > 60–75 ml/min/1.73m^2^, or > 75–100 ml/min/1.73m^2^) and CMV status (low risk vs high risk). Such stratification will ensure to equally allocate patients at high risk of kidney dysfunction in the two groups.

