Perioperative infectious prophylaxis will be based on broad-spectrum antibiotics or adapted to resistance testing. All patients will receive a lifelong *Pneumocystis* prophylaxis with trimethoprim-sulfamethoxazole. Prophylactic inhalation therapy with amphotericin B and refobacin will be provided for 1–3 months. CMV prophylaxis will include CMV hyperimmunoglobulines (POD 1, 7, 14, and 21) together with valganciclovir for a minimum of 3 months. In high-risk patients (donor CMV IgG positive, recipient CMV IgG negative), a 12-month prophylaxis will be performed. Follow-up visits and pulmonary function test will take place once a month during the first year and later every 3 months. Bronchoscopy with transbronchial biopsy (TBB) and bronchoalveolar lavage (BAL) will be performed 1, 2, 3, 6, 12, 24 months after transplantation. A chest computed tomography (CT) will be done once a year. Biopsies will be classified according to ISHLT criteria [44]. ACR grade A2 and LB B2 or higher will be primarily treated with steroids for 3 days with consecutive dose tapering, and in case of non-response, ATG (2 mg/kg) will be administered for 5 days, followed by extracorporeal photopheresis (ECP) if necessary. Kidney insufficiency will be defined as GFR < 60 mL/min/1.73 m^2^ for ≥ 3 months. Infectious complications, including *Aspergillus* infection, will be defined as presence of pathogens with clinical signs and symptoms and need for specific treatment. Donor-specific antibodies (DSA) testing will be performed at each follow-up visit. AMR will be defined according to the ISHLT consensus. Patients with clinical AMR will be firstly treated by plasmapheresis followed by ECP.

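### The reason given for an open-label trial does not cover biopsy grading, so the histological rejection endpoints are left open to avoidable reader bias

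*Protocol article*

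**What the plan says.** All references are to the protocol article.

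- **Trial design {8}** gives the reason for an open design: "Since the dose of immunosuppressive agents will be adapted to reach the blood trough levels, a blinding is not realistically possible".
- **Who will be blinded {17a}** answers for the whole trial: "Blinding is not realistically possible in this academic single-center trial". It then returns to dosing: "An open-label trial allows concentration-controlled administration of immunosuppressant agents, which have a narrow therapeutic index". No role is named as an exception.
- **Procedure for unblinding {17b}** adds "Blinding is not planned".
- **Intervention description {11a}** sets out the histology: "Biopsies will be classified according to ISHLT criteria". It gives a treatment threshold, "ACR grade A2 and LB B2 or higher will be primarily treated with steroids for 3 days", and says of antibody-mediated rejection "AMR will be defined according to the ISHLT consensus". It does not say who reads the biopsies or what the reader is told.
- **Secondary endpoints** are the incidence of ACR, LB, AMR, CLAD and dnDSA, together with survival. The **primary endpoint** is CKD-EPI eGFR at 24 months.
- **Plans for assessment and collection of outcomes {18a}** takes outcome data from routine medical reports and checks that they were entered correctly. Neither masked reading nor adjudication is described.

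**The concern.** The reason offered is about giving drugs. Whoever adjusts tacrolimus or everolimus must see the levels, and the levels reveal the arm. A pathologist assigning an A or B grade adjusts nothing. The decision to blind nobody is therefore wider than the reason behind it.

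This matters because the arms differ in a way that could colour a borderline reading. In Table 2 the tacrolimus target in the treatment arm is 4–5 against 8–10 ng/ml, then 3–4 against 6–8, then 2.5 against 5–7. That is half the control target in the first two cases, and between 2.5/7 = 0.36 and 2.5/5 = 0.50 of it in the last. A reader worried about low exposure may grade up in that arm. A reader who shares the hope, stated in the abstract, of fewer rejection episodes may grade down. Either tendency could create or hide a difference in ACR or LB.

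**Working it through.** The plan gives no figure on this point to reproduce. The check sets each role against the reason given.

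| Role | Must know drug levels to do the task? | Covered by the dosing reason? | Endpoint affected |
|---|---|---|---|
| Patient, treating staff | Yes | Yes | – |
| Pathologist grading biopsies | No | No | ACR, LB, any histological part of AMR |
| Person classifying AMR or CLAD | Not for the classification, but may be on the treating team | Depends on who it is; the article does not say | AMR, CLAD |
| Laboratory result or formula | No judgement of this kind | Not relevant | eGFR, dnDSA |
| Death | No judgement of this kind | Not relevant | Survival |

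**Does the single-centre remark fill the gap?** {17a} mentions the setting but does not say why it would prevent a pathologist from grading without the allocation. It does make accidental unmasking more likely.

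**Is there a safeguard elsewhere?** The double-check in {18a} and the monitoring described in {19} and {23} compare entries with source documents. If the source report carries a shifted grade, these checks confirm it.

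**How the bias would act.** Let the true event rate be *p* in both arms. Let the reader's sensitivity and specificity be Se and Sp, with subscripts T (treatment) and C (control). The expected observed rate in an arm is

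*p*·Se + (1 − *p*)·(1 − Sp).

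With no true difference, the expected treatment-minus-control difference is

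*p*·(Se_T − Se_C) + (1 − *p*)·(Sp_C − Sp_T).

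Three things follow:

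1. The difference is zero when the reader performs equally in both arms, which is what masking aims for.
2. Lower sensitivity in the treatment arm makes it negative, and lower specificity there makes it positive, so the direction is not fixed.
3. The number of patients does not appear, so a larger trial would not reduce it.

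None of *p*, Se or Sp is given in the documents. The expression shows the mechanism and cannot be turned into a size for this trial.

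**The case against.** The case on the other side has real weight.

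- **Scope.** No reader grades the primary endpoint. The sample size, the power and the primary mixed-model test are untouched. This stands, and it limits the point to some of the secondary endpoints.
- **Consistency.** The entry under {17b} is a proper answer for an open-label trial. That is true; the difficulty lies in the reasoning in {8} and {17a}.
- **Unknown readers.** The article does not say who grades biopsies, what the request form shows, or whether readers learn the arm. So bias is possible but not shown. That stands too. Still, this is more than a detail left to a fuller document, because the article gives a flat answer for every role with a reason that fits only some.

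A reader might also infer more than the documents support:

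- *That the rejection results decide whether a kidney benefit is acceptable.* There is no rejection margin or decision rule; rejection is a secondary objective.
- *That A2/B2 defines the endpoint, so one shifted grade alters both outcome and care.* The article uses that cut only to trigger treatment. The endpoint list gives no grade.
- *That masking the readers would remove the bias.* It acts on the reading alone. Open-label decisions, such as whether to take an extra biopsy, remain.
- *That the alphanumeric code already provides masking.* The code is described for randomisation and for stored study data. Nothing says that pathology requests carry it.
- *That an inflated false-positive rate can be quoted.* Every input to such a figure would be assumed.

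**Conclusion.** The concern holds in a limited form. Blinding is ruled out for everyone on a ground that covers patients and treating staff but not the pathologists. ACR, LB and any histological part of AMR are left open to differential grading in either direction. AMR as a whole and CLAD may be exposed too, depending on who classifies them, which the article does not state. eGFR, survival and dnDSA are essentially unaffected.

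No numerical size can be claimed. The conclusion rests on one inference that is not documented: that biopsies can be graded without the allocation and drug levels. Nothing in the article speaks against this beyond the remark about a single centre. The point is a cheap improvement to the secondary rejection results and does not threaten the main analysis.

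**What to change.** 1. In {17a}, and in the matching sentence in {8}, limit the open-label statement to patients and treating staff.
2. State that the existing pathologists grade transbronchial biopsies without allocation or drug levels on the request, and that the grade is recorded before any unblinded discussion.
3. Where existing staff outside the treating team classify AMR and CLAD, have them do so from data without the allocation. Where no such staff exist, say that these endpoints were assessed open-label and report them as such.
4. The trial was already recruiting when the article was written, so record the date from which masked grading applied.

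The cost is a change to the request form and a few sentences of protocol text. Biopsy grading needs no additional reader, and sample size, visits and treatment rules stay as they are. The drawback is that a reader in the same hospital may sometimes learn the arm from the patient record, so masking will be incomplete.

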## Data collection and management

### Plans for assessment and collection of outcomes {18a}

Data will be collected in an electronic case report form on CLINCASE platform (https://www.meduniwien.ac.at/web/mitarbeiterinnen/it-hilfe-support/it4science/plattformen/kss/). The platform has been developed by the Medical University of Vienna and is routinely used in clinical trial performed at our Institution. Data will be collected by [name] and a trained study nurse. All data will be directly taken from official medical reports. All reports will be printed and the correctness of data will be double-checked by [name] and [name]. Moreover, an external monitoring will check the study course.

### Plans to promote participant retention and complete follow-up {18b}

Continuous personal contact with the patients will be established by [name] and our transplant psychologist in order to address possible compliance issue and drop-outs. Based on our preliminary data, a drop-out rate as high as 20% could be expected.

Patients who interrupt the study will undergo the following examinations:
Blood examinations (differential blood count, electrolytes and chemistry, kidney and liver function tests, CRP, LDL, HDL, triglycerides, cholesterol and coagulation status)24 h urinalysisPulmonary function testsECGChest CT scanBronchoscopy with TBB and BALHLA-screeningHistological analysis of TBBMicrobiological analysis of BALBlood CMV count

### Data management {19}

A subject screening and identification Log will be completed for all enrolled subjects with the reasons for exclusion. For this trial, an electronic CRF will be used. Only the investigator or designated sub-investigators will have access to the CRF. A CRF will be created for each subject enrolled. This also applies to those subjects who fail to complete the study. If a subject withdraws from the study, the reason must be noted on the CRF. Case report forms are to be completed on an ongoing basis. In CRF, demographics of the patients, inclusion criteria, randomization group, the medical information from each follow-up visit, adverse events or reason for withdrawal from the study and the EOS visit will be reported. CRF entries and corrections will only be performed by study site staff authorized by the investigator. Data collected at all visits are entered into an interactive form. The eCRFs will be verified source documents, following guidelines established before study onset as detailed in the monitoring plan. The investigator will maintain adequate and accurate records to enable the conduct of the study to be fully documented and the study data to be subsequently verified (according to ICH-GCP “essential documents”). These documents will be classified into two different categories: investigator’s study site file (ISF) with all essential documents regarding the study conduct, and subjects’ clinical source documents. Subjects’ clinical source documents include all patient hospital clinical records in original version. These two categories of documents must be kept on file by the investigator for as long as needed to comply with the regulatory requirements. The designated monitor will contact and visit the investigator on a regularly basis and will be allowed to have direct access to all source documents needed to verify the entries in the CRFs and other protocol-related documents, provided that confidentiality is maintained in agreement with local regulations. It will be the monitor’s responsibility to inspect the CRFs at regular intervals according to the monitoring plan throughout the study, to verify the adherence to the protocol and the completeness, consistency, and accuracy of the data being entered on them. Monitoring visits will be performed every 3 months. Monitoring will be performed by Clinical Trials Coordination Centre. Upon request, the investigator will make all study-related source data and records available to a qualified quality assurance auditor mandated by the sponsor or to competent authority inspectors. The main purposes of an audit or inspection are to confirm that the rights and welfare of the subjects have been adequately protected and that all data relevant for assessment of safety and efficacy of the investigational product have appropriately been reported to the sponsor.

### Confidentiality {27}

All patients’ data will be collected and stored with an alphanumeric code. The code key will be kept in safe custody by the PI and by the personnel designated by the PI. Ethical review committee, national and European health authorities can have access to the data. The investigator will maintain adequate and accurate records to enable the conduct of the study to be fully documented and the study data to be subsequently verified (according to ICH-GCP “essential documents”). These documents must be kept on file by the investigator for as long as needed to comply with the regulatory requirements.

### Plans for collection, laboratory evaluation, and storage of biological specimens for genetic or molecular analysis in this trial/future use {33}

Collected blood will be immediately processed and will be used for FACS analysis and gene expression analysis. Additional blood and BAL sample will be collected and stored as plasma, serum, DNA, and BAL sample in our institutional biobank.

## Statistical methods

### Statistical methods for primary and secondary outcomes {20a}

#### Primary endpoint analysis

An *F*-test for the primary endpoint using mixed model analysis will be performed using the function lme from the R package nlme.

#### Secondary endpoint analysis

Simple ANCOVA analysis for GFR after 12 months and after 24 months, respectively, will be performed.

Chi-square tests, Fisher exact tests, Mann-Whitney *U* tests, or ANOVA will be used to compare differences between the groups. Curves for survival will be generated with Kaplan-Meier method and compared by log-rank tests. A univariate and multivariable Cox regression will be performed to find predictors of survival and CLAD incidence.

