### Outcomes {12}

#### Primary endpoint

eGFR calculated by the CKD-EPI formula at 24 months after transplantation

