### Sample size {14}

#### 110 participants, 55 per group

Sample size calculations are based on available retrospective data of 231 patients treated with our standard protocol (control group). eGFR data are shown for all these patients (left panel) and after 7 outliers were removed who had initial values of eGFR > 220 (right panel).

Our modeling approach assumes that for each patient eGFR strongly drops over the first 6 months and from then on only mildly decreases for the next 6 months. After 12 months, eGFR has stabilized and does not change for each patient till the end of the study after 24 months. The value obtained after 12 months for each patient is modeled as a random intercept. The decrease over the first 6 months differs significantly between patients and is therefore modeled by an additional random effect. To model the longitudinal data, we applied thus the following mixed effects model:
$$ {Y}_{ij}={\beta}_j+{\gamma}_{0i}+{\gamma}_{1i}{c}_j+{\epsilon}_{ij} $$

Index *i* refers to the *i*th individual and index *j* ∈ {1, …, 5} corresponds to the time points 0, 3, 6, 12, and 24 months, respectively. The fixed effects *β*_*j*_ model the average of eGFR at a given time point. $$ {\gamma}_{0i}\sim N\left(0,{\sigma}_o^2\right) $$ is the random intercept and $$ {\gamma}_{1i}\sim N\left(0,{\sigma}_o^2\right) $$ is the random slope for each individual. The (non-linear) random slope is defined by the vector *c* = [1, 0.5, 0.1, 0, 0] which allows each individual to have a different amount of decrease of eGFR within the first 6 months. Consequently, this model allows for more variance (and less correlation between time points) at the beginning of the trial. The final term $$ {\epsilon}_{ij}\sim N\left(0,{\sigma}_{\epsilon}^2\right) $$ corresponds to the normally distributed error term. All random variables specified are assumed to be statistically independent.

Sample size calculations are based on an assumed effect size shown in the next graph. The blue line shows the estimated average behavior of GFR over time for the 224 patients after removing outliers. GFR stabilizes at 60 mL/min. The relevant treatment effect we want to detect is such that GFR stabilizes with the new immunosuppression protocol at 72 mL/min.

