To make best use of the longitudinal data, we are not only testing the difference in GFR between the two treatment groups at 24 months or at 12 months (which could be accomplished by a simple ANCOVA taking the baseline value for each individual as a covariate) but we actually want to compare the whole curves for the two treatments. To this end, we specify a time-dependent effect vector of the form *C*_*eff*_ = [0, 0.5, 0.9, 1, 1] where our main endpoint is the interaction between *C*_*eff*_ and the treatment group. The idea is that initially there is no difference between the two groups while the effect is increasing over the first 6 months and has reached its full amount after 12 months. The following plot presents power curves for this contrast for different group sample sizes and compares with the power of simple ANCOVA analysis of GFR after 12 months or 24 months, respectively.

In the first plot, we simulated exactly under the model described above (the same random effects and the same contrast *C*_*eff*_). The second plot is based on simulations where both the vector *c* defining the random effect as well as the vector *C*_*eff*_ specifying the treatment effect were slightly changed. In both cases, the mixed model (1) was extended to test the interaction between *C*_*eff*_ and treatment at a significance level *α* = 0.05. The power curves (based on 5000 simulation replicates) indicate that the model is fairly robust against slight perturbations of these two vectors and that 45 patients per group are sufficient to detect the specified effect with a power of 80% (we assumed for both groups a covariance structure as given by the preliminary data for the control group). Considering a potential dropout rate of 20% results in a sample size of 55 per group.

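### The only shape-free estimates of the eGFR difference at months 12 and 24 are secondary ANCOVAs limited to patients measured at that visit, though a longitudinal model on all visits would serve better

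*Protocol article*

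**What the plan says.** All references are to the protocol article.

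- **Endpoint** (Outcomes {12}): "eGFR calculated by the CKD-EPI formula at 24 months after transplantation".
- **Primary analysis** (Statistical methods {20a}): an F-"test for the primary endpoint using mixed model analysis will be performed using the function lme from the R package nlme".
- **What it tests** (Sample size {14}): a single-visit comparison is set aside, "but we actually want to compare the whole curves for the two treatments". The tested quantity is one interaction of treatment with C_eff = [0, 0.5, 0.9, 1, 1] over months 0, 3, 6, 12 and 24.
- **Single-visit analyses** (Secondary endpoint analysis): "Simple ANCOVA analysis for GFR after 12 months and after 24 months, respectively, will be performed". The sample size section describes this kind of comparison as one "which could be accomplished by a simple ANCOVA taking the baseline value for each individual as a covariate".
- **Dropout** ({18b}): "Based on our preliminary data, a drop-out rate as high as 20% could be expected". The same 20% takes 45 per group to 55 in Sample size {14}.
- **Missing data** ({20c}): the section anticipates none and gives no method. The modified intention-to-treat set requires only the month 0 and month 3 values.
- **Other analyses** ({20b}): none planned.

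**The concern.** The C_eff coefficient is the 24-month difference only if the effect is flat from month 12 and the weights at months 3 and 6 are right. The document itself gives reason to check this. The Objectives section describes tacrolimus damage to the kidney as continuing to accumulate, and Table 2 changes the trough targets and adds MMF from month 12. An estimate at month 24 that does not impose the shape is the natural check.

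The planned check is a simple ANCOVA on the baseline value. A patient without the month-24 value contributes nothing to it, even with months 3, 6 and 12 recorded. This affects patients inside the modified intention-to-treat set who leave after month 3. The examinations at interruption ({18b}) give a value at exit, not at month 24. If leaving is related to eGFR after baseline, the ANCOVA compares those still measured rather than the groups as randomized. Even if it is not, recorded information is left unused.

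**Working it through.** **1. The plan's own figures.** 45/(1 − 0.20) = 56.25, so 57; 45 × 1.20 = 54; stated 55. This agrees to within two patients per group. The effect is 72 − 60 = 12 mL/min, from "GFR stabilizes at 60 mL/min" and "The relevant treatment effect we want to detect is such that GFR stabilizes with the new immunosuppression protocol at 72 mL/min". The 80% power at 45 per group comes from the plan's simulations. The text gives no variance components, so everything below assumes them and calibrates to that 80%.

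**2. Precision.** 55 × 0.80 = 44 per group with a month-24 value. The ANCOVA standard error rises by √(55/44) = 1.118.

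Example: plateau SD 25.2, random-slope SD 25.2 (equal, as the model is printed), residual SD 12.6.
- Var(month 24) = 25.2² + 12.6² = 793.8
- Var(month 0) = 2 × 25.2² + 12.6² = 1428.8
- Covariance = 25.2² = 635.0
- ANCOVA residual variance = 793.8 − 635.0²/1428.8 = 511.6
- 55 per group: SE = √(2 × 511.6/55) = 4.31; power = Φ(12/4.31 − 1.96) = 0.80
- 44 per group: SE = √(2 × 511.6/44) = 4.82; power = Φ(12/4.82 − 1.96) = 0.70

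With slope/plateau SD ratios of 1–2 and residual/plateau ratios of 0.5–1, ANCOVA power is 0.69–0.82 on 55 and 0.59–0.72 on 44 per group. The primary C_eff test with the same 20% loss keeps 0.84–0.85, but it gains from imposing the shape. The fair comparator is the free month-24 contrast in step 4.

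**3. What the ANCOVA leaves out.** In the example, month 24 correlates 635.0/√(1428.8 × 793.8) = 0.60 with baseline and 635.0/793.8 = 0.80 with month 12. Baseline helps, but the later visits carry more.

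**4. Bias, by simulation from the plan's model.** Settings: 55 per group; true effect 12; c = [1, 0.5, 0.1, 0, 0]; (slope, residual, plateau) SDs of (30, 8, 25.5), (30, 10, 24.5), (40, 12, 21.3) and (30, 15, 21.5). Dropout before months 6, 12 and 24 is logistic in the last observed eGFR (log-odds 1.0–1.5 per SD). The longitudinal contrast has free treatment-by-visit terms, and its covariance is taken as known.

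| Dropout | ANCOVA, month 24 | Longitudinal, month 24 | Power |
|---|---|---|---|
| 20%, unrelated to eGFR | no bias | no bias | 66–76% vs 69–82% |
| 20% overall, same eGFR rule in both arms | 10.8–11.4 | 12.0–12.1 | gap 6–12 points |
| eGFR rule, about 27% control, 12% treatment | 10.1–10.5 | 11.9–12.1 | gap 15–19 points |
| eGFR rule, higher in treatment | 12.2–12.6 | – | – |

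The last row used a partly different set of SDs, including one plateau SD of 49.3. As percentages: (12 − 11.4)/12 = 5% to (12 − 10.8)/12 = 10% too small; 12.5–16% too small; up to (12.6 − 12)/12 = 5% too large.

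**5. Sensitivity to the assumptions.** A second set used (plateau, slope, residual) SDs of (15, 15, 10), (18, 18, 9) and (15, 25, 10), with about 20% lost after month 6. The ANCOVA averaged:
- 11.9–12.0 with random loss;
- 12.0–12.1 when loss depended on eGFR relative to the patient's own arm mean;
- 11.3–11.4 when it depended on absolute eGFR;
- 9.9–10.3 when only control loss depended on eGFR.

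The C_eff coefficient stayed at 12.0–12.1, in data generated with that shape.

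A third set estimated an unstructured covariance, with 15–31% lost (above 20% in the eGFR-dependent cases). The longitudinal month-24 contrast gave 11.8–12.1 with a standard error 2–6% smaller than the ANCOVA's. The ANCOVA was unbiased under random loss and ranged from 8.9 to 13.7 when loss depended on eGFR.

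**The case against.** The strongest reply is that the primary analysis already does what is asked. It is a likelihood-based mixed model on all available visits, it keeps later leavers up to their last value, and C_eff gives full weight to months 12 and 24. Under the plan's plateau assumption its coefficient is the 12- and 24-month difference. This stands: a reader might infer that the trial's main conclusion rests on completers only, and the documents do not support that. The ANCOVAs are secondary, the text claims no power for them, and a simple check that does not depend on C_eff is a reasonable thing to plan. What remains is that this check has the weakest handling of dropout in the plan.

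A reader might also infer that bias is certain, or that the 24-month difference will be understated. No section says that patients with low eGFR leave more often. The specific withdrawal triggers in {11b} are life-threatening rejection or infection and malignancy. They make purely random loss hard to presume, but they do not fix a direction. Under the same rule in both arms the bias of 0.6–1.2 mL/min is below 0.3 of an ANCOVA standard error of about 4.3–5.0, and the 27% versus 12% split is an assumption.

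Two further readings go too far. The 20% is overall dropout, so it should not be applied in full to month 12. Baseline is not uninformative about the plateau: the four main variance sets imply correlations of about 0.4–0.6.

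Handling of missing values may be detailed in an analysis plan that is not shown. But the article fixes the method as a simple ANCOVA and states that missing data are not anticipated, against its own dropout allowance. That conflict is in the text.

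**Conclusion.** The point holds as a cheap improvement to a secondary analysis, not as a flaw in the primary test. The month-12 and month-24 ANCOVAs are the only planned estimates at those visits that do not impose the effect shape, and as written they exclude anyone without that visit.

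The certain cost is modest: a standard error 11.8% larger than with complete follow-up at 20% loss. A longitudinal contrast recovers part of it (a standard error 2–6% smaller than the ANCOVA's when the covariance is estimated). The conditional cost is bias in either direction: none if dropout is unrelated to eGFR, about 5–10% too small under a common absolute-eGFR rule, about 12–18% too small if control loss is higher or only control loss is tied to eGFR (9.9–10.5 against 12), and up to about 5% too large if treatment loss is higher. Heavier loss widens this range. All of these sizes rest on assumed variance components and dropout mechanisms; none can be read from the document.

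**What to change.** In Secondary endpoint analysis, state that the month-12 and month-24 treatment differences, with 95% confidence intervals, come from one longitudinal model on all available visits. It can be fitted in nlme (for example with gls), with visit, treatment-by-visit, baseline eGFR or a common baseline mean, and an unstructured covariance over visits. Keep the two simple ANCOVAs as a labelled sensitivity analysis in patients measured at that visit. In {20c}, reconcile the statement that no missing data are anticipated with the 20% dropout in {14} and {18b}.

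The cost is a few sentences and a few lines of code in the package already named, with no extra data or patients. The downside is more covariance parameters to estimate (15 for five visits, 10 with baseline as covariate) and reliance on data being missing at random given the observed eGFR values. That is weaker than what the ANCOVA needs, but still an assumption to state.
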